### Descriptive statistical analysis

Descriptive statistical analyses will be conducted using IBM SPSS Statistics Software Version 25 (SPSS Inc., Chicago, USA) and the computing environment R4.2.3 (R Foundation for Statistical Computing, Vienna, 2013). The distributions of variables will be assessed using the Shapiro–Wilk test. Patient groups will be characterized using means and standard deviations, medians and interquartile ranges (IQR), frequencies or percentages, and 95% confidence intervals (95% C.I.) for variables with continuous distribution, continuous non-normally distributed variables, and categorical variables, respectively. Depending on the distribution of the data, we will employ ANOVA or non-parametric Kruskal–Wallis tests for between-group comparisons, and Pearson's or Spearman's correlation coefficient to assess correlations between numeric measures of the groups. Chi-square tests will be used to compare categorical data. Effect sizes will be computed using Cohen's *d* for normally distributed numeric measures, η^2^ for the Mann–Whitney-U Test, and Cramer's *V* for categorical data.

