## Methods and analysis

### Study design and participants

This is a longitudinal observational cohort study. We will include consecutive patients who self-referred to the Centre for AD and Adult Cognitive Disorders of Careggi Hospital in Florence and are classified as SCD based on SCD-I criteria [5].

We will recruit patients who meet the following criteria:

Iage between 45 and 90 years;IIcomplaining of cognitive decline with a duration of ≥ 6 months;IIIMini Mental State Examination (MMSE) score greater than 24, corrected for age and education;IVnormal functioning on the Activities of Daily Living (ADL) and the Instrumental Activities of Daily Living (IADL) scales [28];Vunsatisfied criteria for MCI [29] and dementia [30];

Exclusion criteria are history of head injury, current neurological and/or systemic disease, symptoms of psychosis, major depression, or substance use disorder (as defined by the Diagnostic and Statistical Manual of Mental Disorders, Fifth Edition [DSM-5] [30]).

The evaluation of exclusion criteria will be conducted through a thorough neurological examination of the patients. The presence of exclusion criteria will be assessed by two independent neurologists. In the event of a disagreement, a third neurologist will be consulted to reach a consensus.

All recruited patients will undergo the following assessments at baseline (T_0_):Icomprehensive evaluation of familial and clinical history;IIextensive neuropsychological assessment, including estimation of premorbid intelligence, evaluation of depression, personality assessment, and assessment of leisure activities;IIIblood collection for measurement of vitamin B12, folic acid, thyroid hormones, as well as *APOE* and *BDNF* genotype analysis;IVEEG and ERP recording.

Patients who provide additional informed consent for lumbar puncture will undergo CSF collection to measure Aβ_42_, Aβ_42_/Aβ_40_ ratio, total tau (t-tau), and phosphorylated tau (p-tau).

Patients will undergo neuropsychological evaluations every two years until progression to AD or other dementias. Based on the results of previous meta-analysis [8], we estimate that a period of six years will be required to reach the desired sample size (see Sect. 2.2). Progression to MCI and AD dementia will be determined based on the criteria established by the NIA-AA [29, 31]. Patients who progress to dementia will be referred to our centre for diagnostic and therapeutic assessments.

A summary of the study design is shown in Fig. 1.

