### Sample size calculation

We estimated the sample size needed for this study using the statistical power of a hypothesis test using the Python module statsmodels [32]. We considered the following parameters:Level of significance (α) = 0.05Statistical power (1-β) = 0.8Effect size (Cohen's d) = 0.6

The required number of patients was 45 per group. Therefore, considering that we aim to compare patients who will show a progression to objective cognitive decline and patients who will not, the total estimated sample size should be 90 individuals.

With an expected conservative drop-out rate of 10%, the number of participants to be included was estimated to be 99 patients.

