The final statistical analysis will involve extracting microstate maps [61] for each subject individually. Initially, a set of common microstates will be extracted from all subjects, regardless of conditions, using the modified k-means algorithm [62]. Then, individual microstate maps will be generated, and the template maps will be matched with the previously obtained grand-averages. The EEG signals of each subject will be reconstructed as a sequence of microstates by assigning each topography to the most similar microstate average map. From the reconstructed microstate sequence, various metrics such as duration, transition probability, and complexity of the sequence will be used as features. Spectral features, network metrics, and microstate features will be compared across conditions, providing the foundation for the machine learning analysis.

Regarding the ERP data, both spectral features (like the EEG processing) and voltage-level signals (amplitude, latency, integral of the signal) from different phases of the ERP will be used as input features.

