### Machine learning classification of patient conditions

Demographic, clinical, cognitive, neurophysiological, and genetic data will be used as candidate input features without any further processing for training a machine learning model. During the training process, a feature selection algorithm will be applied to select the most informative features based on their performance on the validation set.

The machine learning problem will initially be treated as a multi-class classification task. The model will classify patients who are SCD at the time of the measurements into one of the following three classes: stable SCD, progressed to MCI, or progressed to AD dementia. For the subgroup of patients undergoing CSF biomarker analysis, a classification will be performed based on the results of the analysis. Specifically, patients will be classified as carriers or non-carriers of AD pathology, according to the NIA-AA framework [9].

For feature selection, we will test the efficacy of several algorithms including the ANOVA F-test statistic, ReliefF, mutual information, and minimum redundancy maximum relevance (MRMR). The number of retained features for each algorithm will be optimized in the validation loop.

Regarding the classifier models, a set of different machine learning models will be tested, including support vector machine (SVM) with linear, quadratic, cubic, and radial basis function kernels; random forest (RF); gradient boosted trees (xgboost); linear and quadratic discriminant analysis (LDA and QDA); and an artificial neural network (ANN). The hyperparameters of each algorithm will be optimized to determine the model with the best performance in the classification task.

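### Choosing ANOVA or Kruskal–Wallis by a normality test leaves the reported group comparisons open to unequal variances in outcome-defined groups that will probably differ in size

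*Protocol article*

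**What the plan says.** Under Descriptive statistical analysis, the article first checks normality: "The distributions of variables will be assessed using the Shapiro–Wilk test". It then sets the test: "Depending on the distribution of the data, we will employ ANOVA or non-parametric Kruskal–Wallis tests for between-group comparisons". It names no check of equal variances and no Welch version, so plain ANOVA is read here in its usual sense, the equal-variance F test.

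Three other places bear on this:

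- **How groups arise** (Study design and participants): "We will include consecutive patients who self-referred to the Centre for AD and Adult Cognitive Disorders". Under Machine learning classification of patient conditions, the outcome classes are "stable SCD, progressed to MCI, or progressed to AD dementia". Membership is known only after follow-up.
- **What is powered** (Sample size calculation): progressors against non-progressors at α = 0.05, power 0.8 and d = 0.6. "The required number of patients was 45 per group", so 90 in total, or 99 with drop-out.
- **What the comparisons are for** (EEG Statistical analysis): "Spectral features, network metrics, and microstate features will be compared across conditions, providing the foundation for the machine learning analysis".

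**The concern.** The classical F test pools the group variances. With equal group sizes it tolerates unequal variances well; with unequal sizes it does not. If the smaller group is the more variable, the test rejects too often. If the larger group is, it rejects too rarely and loses power.

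Investigators cannot fix the group sizes here. The article expects about six years to reach its sample, while its Discussion cites an average of ten years from SCD to dementia, so an even split is unlikely. The Shapiro–Wilk step examines the shape of the distribution, not its spread, and the Kruskal–Wallis fallback is itself somewhat sensitive to unequal spread when sizes differ.

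At stake is whether a 5% result in the reported comparisons, including the one the sample size is built on, really is a 5% result.

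**Working it through.** **1. The plan's own figure.** A two-sided t-test with d = 0.6, α = 0.05 and power 0.80 needs n = 44.59, so 45 per group and 90 in total. Then 90 × 1.10 = 99. The stated figures reproduce, on a 1:1 split.

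**2. Inputs.** N = 90 and α = 0.05 come from the article. Splits and SD ratios are assumptions.

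**3. Closed-form check, two groups.**

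- True variance of the mean difference: V = s₁²/n₁ + s₂²/n₂.
- Variance the pooled test uses, on average: P = [(n₁−1)s₁² + (n₂−1)s₂²]/(N−2) × (1/n₁ + 1/n₂).
- Actual level ≈ 2[1 − Φ(1.987 × √(P/V))], where 1.987 is the two-sided 5% point of t with 88 df.

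*72/18, small group SD 1.5, large group SD 1:* V = 1/72 + 2.25/18 = 0.1389. P = (71 + 38.25)/88 × 0.06944 = 0.0862. √(P/V) = 0.788, and 1.987 × 0.788 = 1.566, so the level is about 11.7%.

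*72/18, large group SD 1.5, small group SD 1:* V = 2.25/72 + 1/18 = 0.0868. P = (159.75 + 17)/88 × 0.06944 = 0.1395. √(P/V) = 1.268, and 1.987 × 1.268 = 2.519, so the level is about 1.2%.

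*63/27, small group SD 1.25, large group SD 1:* V = 0.0737, P = 0.0617, √(P/V) = 0.915, so the level is about 6.9%.

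*45/45, any SDs:* P = V exactly, so the level stays near 5%.

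**4. Simulation.** Normal data, equal means, 10,000 runs per row. The article's rule was run with Shapiro–Wilk applied per group at 5%. The last column keeps the rule but puts Welch in the ANOVA branch.

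| Split | SDs | ANOVA | Kruskal–Wallis | Article's rule | Rule with Welch |
|---|---|---|---|---|---|
| 45/45 | 1, 1.5 | 5.1% | 5.3% | 5.3% | 5.3% |
| 72/18 | 1, 1 | 4.8% | 4.8% | 4.9% | 5.1% |
| 63/27 | 1, 1.25 | 6.9% | 6.1% | 7.1% | 5.2% |
| 63/27 | 1, 1.5 | 9.3% | 7.5% | 9.2% | 5.4% |
| 72/18 | 1, 1.25 | 8.9% | 7.0% | 9.0% | 5.6% |
| 72/18 | 1, 1.5 | 12.0% | 7.8% | 11.9% | 5.4% |
| 72/18 | 1.5, 1 | 1.2% | 2.2% | 1.4% | 4.6% |
| 63/20/7 | 1, 1.5, 2 | 20.6% | 11.7% | 19.7% | 6.8% |

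If normality is instead tested on pooled data, the 63/20/7 case gives 15.8%.

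**5. Why the pretest does not help.** With normal data in two groups, about 0.95² = 90% of features pass and go to ANOVA, however different the SDs are.

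**6. Power in the conservative direction.** At 72/18 with SDs 1.5 and 1 and a shift of 0.75, the article's rule has about 52 to 53% power, against 68 to 69% with Welch in the ANOVA branch.

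**The case against.** Several points against this carry weight.

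*The article plans 45 per group, where there is no problem.* True, but that is a sample-size assumption that consecutive recruitment cannot enforce. Unequal groups are a sound inference from outcome-defined membership; they are not a stated design feature.

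*The article gives no SDs.* Correct. It calls SCD heterogeneous in trajectory and cause, which says nothing direct about the spread of any feature by outcome. A mixed stable group could equally be the more variable one, and that is the conservative direction. A reader might take 1% or 20% as the expected error rate; the documents do not support that.

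*The comparisons are labelled descriptive.* This limits the consequence. A reader might infer that false predictors enter the classifier or real ones are dropped. The article describes no such route: features are selected by separate algorithms on validation performance, and the chosen model is assessed on a 30% test set. The sentence calling the feature comparisons the foundation of that work sets no significance filter. The conditions it mentions may also include the healthy-control and MCI samples, whose sizes are not given.

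*Effect sizes change scale with the normality result.* They do, between Cohen's d and η², but the article proposes no ranking of features by effect size, so nothing is shown to go wrong.

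*Welch everywhere would be worse.* This stands. With identical skewed distributions in groups of 63/20/7, Welch's ANOVA rejects about 11.8% (lognormal) and 9.9% (exponential), while the article's rule stays between about 4% and 5%. The remedy has to be narrower than Welch for all continuous features.

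**Conclusion.** The point holds in a limited form. The stated rule has no protection against unequal variances, and the groups it will be applied to are probably unequal in size. For 63/27 to 72/18 and SD ratios of 1.25 to 1.5, a nominal 5% comparison runs at about 7 to 12% when the smaller group is more variable. In the opposite direction it drops to about 1.5% at 72/18 with ratio 1.5, with roughly 16 points of power lost for a 0.75 shift. About 20% arises only in the extreme three-group case. With equal variances the level is about 5% at any split.

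All of this rests on assumed splits and SDs and on normal data. It concerns the reported group comparisons, including the progressor comparison used for the sample size. It is not evidence of bias in the classifier or its test-set performance. A small correction is worth making because it is cheap.

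**What to change.** In Descriptive statistical analysis, replace classical ANOVA with Welch's ANOVA (Welch's t-test for two groups) for approximately normal features. Keep a rank test for skewed features; for two groups use Brunner–Munzel, which tolerates unequal spread. State that Welch is not applied to untransformed skewed features.

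**Cost.** One sentence of text. If variances are equal, about 1 to 2 points of power: at 72/18 with d = 0.6, 61.7% under the article's rule against 60.0% with Welch in the ANOVA branch. With a very small third group Welch is slightly liberal, about 6 to 7% in the extreme 63/20/7 case. For skewed features in three groups Kruskal–Wallis remains, with its own sensitivity to unequal spread, so those results should be read with the group SDs or IQRs beside them.

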### Machine learning classification of patient conditions

Demographic, clinical, cognitive, neurophysiological, and genetic data will be used as candidate input features without any further processing for training a machine learning model. During the training process, a feature selection algorithm will be applied to select the most informative features based on their performance on the validation set.

The machine learning problem will initially be treated as a multi-class classification task. The model will classify patients who are SCD at the time of the measurements into one of the following three classes: stable SCD, progressed to MCI, or progressed to AD dementia. For the subgroup of patients undergoing CSF biomarker analysis, a classification will be performed based on the results of the analysis. Specifically, patients will be classified as carriers or non-carriers of AD pathology, according to the NIA-AA framework [9].

For feature selection, we will test the efficacy of several algorithms including the ANOVA F-test statistic, ReliefF, mutual information, and minimum redundancy maximum relevance (MRMR). The number of retained features for each algorithm will be optimized in the validation loop.

Regarding the classifier models, a set of different machine learning models will be tested, including support vector machine (SVM) with linear, quadratic, cubic, and radial basis function kernels; random forest (RF); gradient boosted trees (xgboost); linear and quadratic discriminant analysis (LDA and QDA); and an artificial neural network (ANN). The hyperparameters of each algorithm will be optimized to determine the model with the best performance in the classification task.

In the SVM, the parameters C (misclassification penalty) and gamma (influence of single training points) will be optimized. For the RF, the number of trees (estimators), maximum depth of each tree, and minimum number of data points allowed in a leaf node will be optimized. The same hyperparameters will be tuned for xgboost, along with the learning rate of the algorithm. In LDA and QDA, the type of solver used by the algorithm and the shrinkage term will be adjusted. For the ANN, the number of layers and neurons per layer will be optimized. We have chosen to compare feature selection methods from classical statistics (such as ANOVA F-test) with data-driven methods (ReliefF and MI) that do not assume the distribution of the data. Additionally, the MRMR algorithm will be tested to consider possible redundancies among features.

In the machine learning models, both linear (linear SVM and LDA) and non-linear (polynomial and radial basis function [RBF]-SVM and QDA) algorithms that define separating hyperplanes will be tested, along with tree-based methods like RF and xgboost. The ANN will serve as a non-linear, black-box model to assess the discrimination performance and potential overfitting of more complex models. Furthermore, standard dimensionality reduction techniques will be applied to extract the most salient features. The procedure described above will be repeated to evaluate whether similar results can be achieved with a subset of the features. Once the cross-sectional classification is performed, longitudinal data will be utilized to develop an algorithm capable of predicting the future progression of cognitive impairment.

Out of the entire dataset, 30% of the data will be reserved as a testing set, while the remaining 70% will be used for training and validation of the model. A fivefold cross-validation approach will be employed to train and optimize the hyperparameters of the models. The best performing model, determined by the prediction F1-score and the set of optimized hyperparameters, will be tested on the testing set to obtain an unbiased estimate of the model's performance.

A visual summary of the data collection and analysis process is shown in Fig. 2.

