### EEG Statistical analysis

Firstly, we will calculate the power spectral density (PSD) of the signal recorded in each channel using the Welch's method. The PSD will be computed on continuous windows of EEG signals, applying Hanning windows with no overlap. The spectrum will be divided into four canonical frequency bands: delta (1–4 Hz), theta (4–8 Hz), alpha (8–13 Hz), and beta (13–30 Hz). The scalp will be divided into six regions of interest (ROIs): frontal right (Fp2, AF4, AF8, F2, F4, F6, F8), frontal left (Fp1, AF3, AF7, F1, F3, F5, F7), central right (FC2, FC4, FC6, FT8, C2, C4, C6, T4, CP2, CP4, CP6), central left (FC1, FC3, FC5, FT7, C1, C3, C5, T3, CP1, CP3, CP5), occipital right (P2, P4, P6, T6, PO8, PO4, O2), and occipital left (P1, P3, P5, T5, PO7, PO3, O1). ROI power will be computed as the average relative power from channels belonging to each ROI.

Next, we will analyse the connectivity between pairs of ROIs using LORETA source-reconstructed signals and extract several network metrics from the weighted undirected adjacency matrices. These metrics will include the average strength of connectivity among pairs of ROIs (mean weight of non-zero connections), the weighted clustering coefficient (C) and the weighted characteristic path length (L) [60]. Finally, we will compute the small-world coefficient [57]:$$\Omega = \frac{Lr}{L}- \frac{C}{Cl}$$where L and C are the previously computed weighted clustering coefficient and weighted characteristic path length, whereas Lr is the weighted characteristic path length of an equivalent random network and Cl is the weighted clustering coefficient of an equivalent lattice network.

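### Feeding features to the models unprocessed handicaps the scale-dependent learners (SVM, neural network, shrunken LDA/QDA) in the planned model comparison

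*Protocol article*

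**What the plan says.** The section *Machine learning classification of patient conditions* of the protocol article states that all the collected data types "will be used as candidate input features without any further processing for training a machine learning model". It then sets out the following.

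- **Selection:** four filters are tried (ANOVA F-test, ReliefF, mutual information, MRMR), with the number of features kept tuned in the validation loop. The caption of Fig. 2 confirms that selection comes before the classifier.
- **Classifiers:** "support vector machine (SVM) with linear, quadratic, cubic, and radial basis function kernels", plus random forest, xgboost, LDA, QDA and a neural network.
- **Tuning:** for the SVM, "the parameters C (misclassification penalty) and gamma (influence of single training points) will be optimized"; for LDA and QDA, "the type of solver used by the algorithm and the shrinkage term will be adjusted".
- **Dimensionality reduction:** planned in the same section, with no method named.
- **Choice of model:** the best F1-score in fivefold cross-validation on 70% of the data, then one test on the other 30%.

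The inputs are on very different scales. For EEG, "ROI power will be computed as the average relative power from channels belonging to each ROI", so these features lie between 0 and 1. For the ERPs, "voltage-level signals (amplitude, latency, integral of the signal) from different phases of the ERP will be used as input features", and *EEG and ERP recording* sets an epoch ending 1000 ms after the stimulus. Elsewhere the article lists age from 45 to 90, personality factors of 24 five-point items each, leisure activities rated 0 to 5, Trail Making A and B, and *APOE* and *BDNF* genotypes. No section mentions scaling or genotype coding.

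**The concern.** An article may leave scaling to the full analysis plan. This one states a rule that, on its face, excludes it, so an analysis plan that standardised the inputs would depart from the published text.

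Kernel SVMs work on distances or inner products of the feature vectors, so a feature measured in large units counts for more whatever its information content. A neural network and shrunken discriminant analysis also depend on units, through the gradient or the penalty. Tuning one common gamma stretches all features together and cannot rebalance them.

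Two of the study's questions are exposed. One is whether EEG, ERP and genotype features help to predict progression. The other is which family of models performs best. If the inputs are left in raw units, part of the answer reflects units of measurement, and the F1 ranking favours the methods that do not depend on them.

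**Working it through.** **Design figures.** The plan gives no figure on this point. Its sample size fixes the scale of the problem and reproduces: a two-sided t-test with d = 0.6, alpha 0.05 and power 0.80 needs 44.59, hence 45 per group and 90 in total; 90 × 1.1 = 99. The training share is 0.7 × 99 = 69.3, so 70 records are used below.

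**Step 1: share of squared distance, from the document's ranges.** For two independent patients the expected squared difference on feature j is twice its variance, so its share is variance_j / sum of variances. Assume uniform spread over each range (variance = range²/12), personality items scored 1 to 5 (24 to 120), nine intellectual activities summed (0 to 45), and genotype indicators with prevalence 0.3 (variance 0.3 × 0.7 = 0.21). One feature of each kind:

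| Feature | Variance | Share |
|---|---|---|
| Personality factor | 96²/12 = 768 | 69.4% |
| Age | 45²/12 = 168.75 | 15.3% |
| Leisure score | 45²/12 = 168.75 | 15.3% |
| Relative power | 1/12 = 0.083 | 0.008% |
| *APOE*, *BDNF* indicators | 0.21 each | 0.02% each |

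**Step 2: the same with assumed SDs.** Age 8, personality 10, leisure 7, relative power 0.08, genotypes as above. The sum is 64 + 100 + 49 + 0.0064 + 0.42 = 213.43. Relative power has 0.0064/213.43 = 0.003% and each genotype 0.21/213.43 = 0.10%. Add ERP latency with SD 40 ms (variance 1600): latency takes 1600/1813.43 = 88.2%, relative power 0.0004%, each genotype 0.01%. Record the same latency in seconds (variance 0.0016) and its share is 0.0016/213.43 = 0.00075%. Only the unit has changed.

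**Step 3: after selection.** If a filter keeps only two relative-power features and the e4 indicator, the shares are 0.0064/0.2228 = 2.9%, 2.9% and 0.21/0.2228 = 94.3%. The imbalance has reversed, but units still set it.

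**Step 4: which steps are immune.** On simulated data with features multiplied by factors from 0.001 to 1000, every ANOVA F value was unchanged (for example 15.234 both times), and so was every ReliefF weight computed with the usual division by feature range. Only an unnormalised ReliefF depends on units. Tree methods and unshrunken LDA/QDA do not.

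**Step 5: loss in discrimination.** A radial-kernel least-squares classifier was trained on 70 records, with gamma and C tuned by fivefold cross-validation. The assumed SDs were of the order of 60 s for Trail Making B, 40 ms for latency, 9 for word-list recall and age, and 0.08 for relative power. Signal was placed in four power features at d = 0.6 plus *APOE* carriage, and in a second scenario also in one latency and one Trail Making feature. Entries are out-of-sample AUC, raw versus standardised. Where several pairs appear, they come from separate runs that differ in details such as the selection grid and the number of repeats.

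| Pipeline | Signal in small-unit features only | Signal also in large-unit features |
|---|---|---|
| No selection | 0.50 v 0.72 | 0.63 v 0.76 |
| F-based selection | 0.57 v 0.71; 0.65 v 0.71; 0.67 v 0.72 | 0.65 v 0.79; 0.66 v 0.75 |
| Principal components | 0.50 v 0.68 | 0.62 v 0.75 |

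With selection, as planned, the gaps run from 0.72 − 0.67 = 0.05 to 0.71 − 0.57 = 0.14. Without it, and with signal in small-unit features only, the gap is 0.22. A separate seven-feature set-up without selection (shifts of 1 SD in two power features, e4 frequency 20% versus 50%) gave 0.58 v 0.81.

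**The case against.** The best reply has four parts.

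**Selection comes first.** The filters can drop uninformative large-unit features before the SVM sees them. This stands in part. In the run most favourable to it, selection cut the loss from 0.22 to 0.05. A reader might infer from the rule that the SVM would ignore EEG power and genotype altogether. That does not hold for the planned pipeline, and a linear SVM or a neural network can partly offset units through its weights. But a large-unit feature that is itself informative will be kept, and it then dominates the kernel.

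**The phrase is shorthand.** *EEG pre-processing* and *EEG Statistical analysis* describe extensive processing, so the wording may mean only that nothing is added after feature extraction. The planned dimensionality reduction also shows that a total ban was not meant. This is fair, but scaling comes after extraction, the neuropsychological and genetic data have no extraction step in which it could sit, and no section restores it.

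**The held-out test is sound.** A handicapped SVM would simply not be chosen, and the test-set estimate is not biased by scaling. This stands. The damage is to the comparison between model families and to what is concluded about EEG and genotype within the scale-dependent ones.

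**Wider readings fail.** One might infer that ReliefF is distorted; in its usual form it is not. One might infer that imputation is banned and incomplete records are lost. The article is silent on missing data, a matter normally left to the analysis plan, and xgboost can accept missing values. Nor does the article say that genotype codes would be entered as ordinary numbers.

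**Conclusion.** The point holds in a limited form. As worded, the rule omits scaling for the linear, polynomial and radial SVMs, the neural network, shrunken LDA/QDA and any scale-dependent dimensionality reduction, on inputs whose variances differ by several orders of magnitude. The F1 comparison then leans towards random forest and xgboost. With the planned selection, the radial-kernel loss is roughly 0.05 to 0.14 in AUC; it is about 0.2 only if selection is left out and all signal sits in small-unit features.

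These sizes rest on assumed SDs, effect sizes and carrier rates, on Trail Making and latency entering as raw seconds and milliseconds, and on AUC from a least-squares kernel classifier rather than the plan's three-class F1-score. The direction does not depend on those choices; the amount does. The sample size and the validity of the test-set estimate are unaffected. It should be corrected because doing so is nearly free, but it does not threaten the study as a whole.

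**What to change.** In *Machine learning classification of patient conditions*, replace the phrase about no further processing with:

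> Within each training fold, continuous features are standardised and genotypes are coded as indicators; the fitted transformations are applied unchanged to the validation and test data.

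For the final model, the training data are the full 70% set, and the 30% test set is transformed with those estimates. In the same edit, reconcile the sentence with the dimensionality reduction announced later in the section: name the method and say that it acts on the standardised features inside the same fold.

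The cost is one sentence and a standard pipeline step. No new data are needed and the sample size does not change.
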